#### Music and control interventions

2.3.3

Most studies on music interventions show high heterogeneity in music selection. Based on earlier research, it is challenging to determine the optimal combination of music and setting that works best for each individual [16]. Some evidence suggests that having more freedom to choose music and listening to preferred music is superior [[17], [18], [19],^42^]. Moreover, several (clinical) studies exclusively use classical and/or ‘relaxing’ ambient music, following the cultural belief that this music might be superior in reducing pain [[43], [44], [45]]. However, no substantial evidence supporting this belief has been found so far. Therefore, subjects will receive two different types of music intervention (self-chosen and researcher-chosen) and a neutral, informative podcast as a non-music control condition. Each intervention will last 20 min before pain endurance is tested. Standardized instructions will be utilized to introduce the three interventions and explain the study procedure to the participants. Due to the nature of the study and the music intervention, it is not possible to blind participants and investigators.

The self-chosen music will be selected by the participants in advance. The researcher-chosen playlist will be created by the Music as Medicine research group from Erasmus Medical Center. The playlist will be created with the goal of reducing pain perception based on previous literature [5,18,26,46]. An overview of the researcher-chosen music can be found in Appendix B. The selection of the podcast is guided by two factors: 1) ensuring the content is entirely non-musical (i.e., comprising only voice or conversation), and 2) ensuring the content is neutral, devoid of political, ideological, or cultural subjects. Therefore, participants will be listening to an informative podcast about flora and fauna which makes no mention of climate change or other obvious topics that may elicit strong emotional reactions and/or political polarization.

### Measurements

2.4

#### Pain endurance

2.4.1

The primary outcome of this study is pain endurance, quantified in amperage, through increasing electric stimuli administered at the end of each intervention (self-chosen music, researcher-chosen music, and control). The electric stimuli will be administrated by the STMISOLA (Biopac Systems Inc. Goleta, CA, USA). Two electrodes will be attached to the index finger of the non-dominant hand. Administration of the electrical pulses with a frequency of 100 Hz will start when the participants press a button with the other, dominant hand. When this button is pressed, electric pulses with a current increase rate of 0.5 mA/s will be administered up to a maximum of 30 mA for safety reasons.

When the experiment starts and the participant is connected to the device, the sensation threshold will be tested. At the end of each intervention, while the participants are still listening to music or the podcast, the pain endurance will be tested. Standardized instructions will be used, instructing participants to tolerate the electric pain stimuli as long as possible. Each measurement will be repeated three times, and the average amperages will be registered.

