Currently, there is no consensus about which music works best for which patient. Previous research investigated the psychophysiological effect of self-chosen music, highlighting the importance of individual preferences [20]. While research on pain (management) is increasingly sensitive for socio-cultural differences [21,22], research on MIA notably lacks consideration for socio-cultural background characteristics such as level of education, age or ethnicity. Sociological studies have established that these characteristics – cultural capital as a trait of level of education most specifically – act as key factors contributing to musical taste differentiation [[23], [24], [25], [26], [27]] and music perception [28,29]. Moreover, these factors affect musical taste patterns, which in turn are closely aligned with listening experience and social identity, in which musical taste plays a significant role as well [30,31]. For example, people who have enjoyed higher education levels are typically much more inclined to like ‘highbrow’ music such as classical or jazz [24,26], which also prescribe different behaviors – e.g. sitting, contemplation, not singing along – during listening and concerts than less ‘legitimate’ music preferences such as rap, schlager or heavy metal [32]. As a consequence, these socio-cultural background characteristics can potentially affect MIA [26,27], which is why this should be considered when investigating the therapeutic effects of music on pain.

This study aims to investigate whether the effect of (preferred) music on pain endurance remains consistent across different socio-cultural backgrounds. With this study, we will combine knowledge from different disciplines by integrating sociological methods into medical research, which could provide new perspectives on music as medicine. The MOSART study adopts a cross-over design, wherein every participant will undergo three distinct interventions in a randomized sequence: 1) self-chosen music, 2) researcher-chosen music, and 3) a neutral spoken-word podcast as a control condition. Following each intervention, participants will be subjected to increasing electric stimuli to assess changes in pain endurance.

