### Data management and statistical analysis

2.5

Data will be managed using Castor EDC (Ciwit B·V., Amsterdam), a certified data capture tool that includes skips, validation checks and an audit trail. This study will look at the influence of (preferred) music on MIA across different socio-cultural backgrounds (through an explorative approach. For normally distributed data, we plan to utilize a linear mixed model to analyze both the primary outcome (pain endurance) and secondary outcomes (pain intensity and unpleasantness, HRV, SAM, STAI-6). In the fixed-effects part of the model the following effects will be included: intervention, position within randomization sequence, age, TRAIT anxiety, level of education, economic capital (income), participants' cultural capital, parents’ cultural capital and ethnicity. Interaction terms such as intervention and position within randomization sequence will eventually be included using F and likelihood ratio test. In the random-effects structure we will incorporate random intercepts and a random effect of the time point of sequence. Because of the continuous measurement of HRV during each intervention the time point (within each intervention) will be included as fixed and random effect. This way, we will consider the period effect and potential carry-over effects of the cross-over study design. In the event of not normally distributed data a Friedman test will be performed instead. Moreover, subgroup analyses excluding participants with maximal pain endurance during all three interventions and non-adherence to the protocol will be performed. Data analysis will be performed using R version 4.0 or higher.

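### Pain endurance is right-censored at 30 mA but modelled as exact: this attenuates the music effect in mA and, if cap shares differ by education, can make an equal effect look unequal

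*Protocol article*

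**What the plan says.** Section 2.4.1 (Pain endurance) defines the endpoint: "The primary outcome of this study is pain endurance, quantified in amperage". The current rises steadily to a ceiling: "electric pulses with a current increase rate of 0.5 mA/s will be administered up to a maximum of 30 mA for safety reasons". The standard instruction is described as "instructing participants to tolerate the electric pain stimuli as long as possible". On recording, the section says: "Each measurement will be repeated three times, and the average amperages will be registered".

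Section 2.5 (Data management and statistical analysis) gives the model for normally distributed data: "we plan to utilize a linear mixed model to analyze both the primary outcome (pain endurance) and secondary outcomes". Otherwise: "In the event of not normally distributed data a Friedman test will be performed instead". The only provision for the ceiling is an extra analysis: "subgroup analyses excluding participants with maximal pain endurance during all three interventions and non-adherence to the protocol will be performed". Censoring is not mentioned.

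The Background puts the study question as "whether the effect of (preferred) music on pain endurance remains consistent across different socio-cultural backgrounds". Recruitment and randomization are stratified by education, with 28 participants in each of three strata.

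**The concern.** A reading of 30 mA is a lower bound. If music raises the endurance of someone who already reaches 30 mA under the podcast, the instrument cannot show it. If music lifts someone from 28 mA to what would have been 34 mA, only 2 of the 6 mA are seen. A linear mixed model on the amperage therefore estimates the effect on capped endurance, which is smaller than the effect on endurance itself.

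The shrinkage grows with the share at the cap. The study asks whether the effect is the same across backgrounds, so unequal cap shares matter more here than in a plain comparison of music with podcast: strata with the same true effect would show different measured effects.

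The authors foresee participants at the maximum in all three interventions, so the ceiling is an expected feature of the data. The analysis they name for it selects participants on the outcome and leaves in, uncorrected, everyone capped in only one or two interventions.

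**Working it through.** **Inputs from the article.** Cap 30 mA; ramp 0.5 mA/s, so the cap is reached after 30/0.5 = 60 s if the ramp starts at zero; three readings per intervention, averaged; 84 participants in 3 strata of 28; Cohen's d 0.4; two-sided 5%; 90% power.

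**Inputs assumed, because the article gives none.** Latent endurance normal with SD 1; both music conditions 0.40 SD above the podcast; share at the cap under the podcast 5% to 40%; ICC 0.5 or 0.8.

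**Plan's own figure.** The article gives no figure on the cap. Its total of 84 cannot be reproduced without the ICC and dropout values, but is plausible: n = 2(1 − ICC)(1.960 + 1.282)²/d² with ICC 0.5 gives 10.51/0.16 = 65.7, so 66, and 66/0.8 = 82.5, so 83 with 20% dropout.

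**1. Attenuation.** For Y ~ N(μ, 1) capped at c,

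E[min(Y, c)] = μΦ(c − μ) − φ(c − μ) + c[1 − Φ(c − μ)].

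With 20% capped under the podcast, c = 0.8416.
- Podcast (μ = 0): −0.2800 + 0.8416 × 0.20 = −0.112.
- Music (μ = 0.40): 0.40 × 0.6706 − 0.3619 + 0.8416 × 0.3294 = 0.184.
- Difference: 0.295, which is 74% of 0.40.

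| Capped under podcast | Expected estimate (SD) | Share of 0.40 |
|---|---|---|
| 5% | 0.370 | 92% |
| 10% | 0.343 | 86% |
| 15% | 0.319 | 80% |
| 20% | 0.295 | 74% |
| 30% | 0.250 | 63% |
| 35% | 0.229 | 57% |
| 40% | 0.208 | 52% |

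**2. Overall test (simulation, 84 completers, self-chosen music versus podcast).** At ICC 0.5, power falls from 0.95 without a cap to 0.94, 0.91, 0.88 and 0.83 with 10%, 20%, 30% and 40% capped. At ICC 0.8 it stays at 0.99 or above. With no true effect, rejection stays near 5%, with and without the exclusion.

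**3. Excluding those at the maximum in all three interventions.**

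| Capped under podcast | ICC | Excluded | Estimate before | Estimate after |
|---|---|---|---|---|
| 10% | 0.5 | 3% | 0.34 | 0.35 |
| 20% | 0.5 | 9% | 0.30 | 0.32 |
| 30% | 0.5 | 16% | 0.25 | 0.30 |
| 20% | 0.8 | 15% | 0.30 | 0.35 |

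The estimate moves towards 0.40 but does not reach it. With 20% capped, participants capped in one or two interventions carry about 83% of the lost effect at ICC 0.5 and 60% at ICC 0.8. All of them stay in.

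**4. Education strata with the same true effect of 0.40 (28 per stratum, two-sided 5% test of first versus last stratum on the within-person difference).**
- 5% versus 35% capped: measured effects 0.37 and 0.23, a spurious gap of 0.14. Rejection about 10% at ICC 0.5 and 16% at ICC 0.8.
- 5% versus 15% capped: 0.37 and 0.32, a gap of 0.05. Rejection 5% to 6%.
- Three-stratum F-test with 5/20/40% capped: measured effects 0.37/0.30/0.21. Rejection 10.7% at ICC 0.5 and 19.3% at ICC 0.8.
- Equal cap shares, or no music effect: near 5%.

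**5. Averaging.** Readings of 30, 30 and 24 mA average to 28, which looks uncensored. With 20% of readings capped and a within-condition reading SD of 0.2 to 0.5, between 9.5% and 24% of averages mix capped and uncapped readings, and the average alone does not reveal it.

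**6. Does a censored model repair it?** A random-intercept Tobit model at ICC 0.5 with 5/20/40% capped gave a pooled effect of 0.396 (Monte Carlo SE 0.008), against 0.290 uncensored. The false education-by-intervention rate was 4%, but from only 150 runs, against 10.7% uncensored.

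**The case against.** Several points on the other side are sound.

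- **The linear model applies only to normally distributed data.** Heavy capping may send the analysis to the Friedman test, which sees capped values as ties and is less affected. This stands, and the attenuation figures do not carry over to that branch. But the Friedman test cannot model education, so it cannot answer the consistency question.
- **The exclusion is an additional subgroup analysis.** A reader might infer that it defines the primary result, or that it is what shrinks the effect. Neither is so: the cap causes the shrinkage, and the exclusion moves the estimate towards the truth. Its faults are that it selects on the outcome and corrects too little.
- **A reader might infer that single readings are discarded.** The article says that averages are registered, not that nothing else is kept, and it condenses a fuller protocol. The censoring problem does not depend on this point.
- **The harm to the overall test is small.** Capping also reduces within-person variance. With 20% capped and ICC 0.5, the effect divided by the SD of the paired difference falls from 0.40 to about 0.36, much less than the 26% loss in the estimate itself.
- **Nothing in the article shows that cap shares differ by education.** This stands. With a mild gradient the false-difference rate is close to nominal.
- **The socio-cultural analysis is declared exploratory.** This lowers the stakes but does not remove the bias, and consistency across backgrounds is the stated aim.

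**Conclusion.** The concern holds in a limited form. The planned linear mixed model treats a right-censored endpoint as exact, so its estimate of the music effect in mA is biased towards zero whenever a meaningful share of readings reaches 30 mA. The planned exclusion repairs this only in part.

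The distortion of the education comparison is conditional. It needs a real music effect and clearly unequal cap shares. A reader might conclude that the plan will produce false education differences, or that the overall test is invalid. The article supports neither: it reports no cap share, the overall null test keeps its level, and the power loss is modest unless capping is heavy.

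All sizes rest on latent normality, a 0.40 SD effect and assumed cap shares and ICCs. The direction is firm, the size unknown. The change is worth making because it is cheap and bears on the study's main question.

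**What to change.** 1. Leave the safety cap unchanged.
2. Keep the three single readings per intervention, each with a flag for reaching 30 mA, if this is not already done. Section Trial status reports 50 enrolled by 1 March 2024, so 84 − 50 = 34 remained at that date. For those already enrolled, recover single readings from device or source records where they exist.
3. Fit a mixed model right-censored at 30 mA (Tobit) with the planned fixed effects, for the intervention and intervention-by-education estimates. If single readings are modelled, add a participant-by-intervention random effect. Report it beside the uncensored model.
4. Report the share at the cap by intervention and education, so that readers can judge how much the two models should differ.
5. Label the exclusion of always-maximal participants as descriptive only.

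The cost is a few extra data fields and a different likelihood in R. The downside is reliance on the latent-normal assumption beyond 30 mA, where no data exist. Showing both models makes that dependence visible. Where only averages survive, mixed averages cannot be flagged, and the censored model is then an approximation for those participants.

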#### Stratification and randomization

2.3.1

Current sociological literature provides evidence that humans are differently socialized regarding music taste and music perception [[23], [24], [25], [26], [27],[34], [35], [36]]. Stratified recruitment and randomization (Castor EDC, Ciwit B·V., Amsterdam) based on level of education will be performed to ensure maximum variation in educational levels in our sample. Since level of education is a key indicator of cultural capital [37], which in turn plays a significant role in shaping individual musical preferences, stratification will be based on participants’ level of education [34]. Thus, the study population will consist of 1/3 less-educated, 1/3 medium-educated, and 1/3 more-educated female subjects. This categorical strategy was chosen because other groupings, such as years of education, are less suitable in the Dutch education system, where students are separated into different educational tracks at the age of 12. A comparison between these three categories will allow us to compare participants belonging to clearly defined educational groupings and thus assess the impact of schooling level as a proxy for cultural capital. An overview of the stratification strategy by level of education can be found in Appendix A.

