#### Psychological questionnaires

2.4.3

In addition to the objective pain endurance, as measured in amperage, participants will be asked to rate the pain intensity and pain unpleasantness using an 11-point Numeric rating scale (NRS), where 0 implies no pain and where 10 implies the worst pain imaginable [52]. Since pain is a highly subjective experience, measuring (changes in) emotions is essential in pain assessment [53]. Anxiety will be measured with the State-Trait Anxiety Inventory (STAI-6) at baseline and after each intervention [54,55]. This questionnaire consists of six items and is a validated and frequently used method (Cronbach's α 0.83) [56]. Furthermore, the participants' emotions will be assessed with the Self-Assessment Manikin (SAM) at baseline and after each intervention. The SAM is a validated non-verbal pictorial assessment technique that directly assesses the emotional valence (Cronbach's α 0.73) and arousal (Cronbach's α 0.98) associated with a person's affective response to a wide variety of stimuli [57,58]. Moreover, the personal experience of listening to music and the podcast will be evaluated at the end of the experiment with five open-ended questions. This evaluation aims to account for confounders and to elaborate upon any interaction(s) between personal experience, music perception and pain endurance.

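### The pre-intervention sensation threshold is left out of the pain endurance model, so the exploratory main effects of education and background are less precise than they could be and open to differences in electrical sensitivity

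*Protocol article*

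**What the plan says.** Section 2.4.1 (Pain endurance) places the threshold measurement at the start of the session, before the first intervention: at that point "the sensation threshold will be tested". The same section defines the outcome on an absolute scale: "The primary outcome of this study is pain endurance, quantified in amperage". Endurance is not expressed relative to each participant's threshold.

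Section 2.5 (Data management and statistical analysis) spells out the fixed effects of the linear mixed model: "intervention, position within randomization sequence, age, TRAIT anxiety, level of education, economic capital (income"), followed by participants' and parents' "cultural capital and ethnicity. Interaction terms such as intervention and position within randomization sequence will eventually be included". Random intercepts and a random effect of time point complete the model. The sensation threshold does not appear, and the article states no other use for it.

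Section 2.3.1 (Stratification and randomization) says that the three education categories let the team "compare participants belonging to clearly defined educational groupings" and so judge the impact of schooling. Section 2.2 plans 28 participants per category. Sections 2.5 and 3.3 call the sociological part exploratory.

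For the secondary outcomes, section 2.4.3 has STAI-6 and SAM measured "at baseline and after each intervention". The fixed-effects list contains trait anxiety but does not name the baseline score of either instrument as a covariate for its own outcome.

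**The concern.** The model has two kinds of terms. Intervention contrasts are made within participants, so a stable personal level of sensitivity to current cancels. Main effects of education, income, cultural capital and ethnicity are made between participants, so it does not cancel. A random intercept accounts for that variation but does not explain any of it.

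The sensation threshold is a measure of sensitivity taken on the same device before any exposure. Leaving it out has two possible consequences for the background main effects:

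- **Precision.** Their standard errors stay larger than they need to be, in strata of only 28.
- **Interpretation.** Education is not randomised. If strata differ in sensitivity to current or in electrode contact, the unadjusted education coefficient includes that difference, and a reader would see it as an effect of schooling.

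The protocol's own reasoning points the same way. Section 2.3.2 restricts sex and age because pain tolerance is heterogeneous. Section 3.3 says that enrolling only women keeps conclusions about background indicators feasible. Section 2.5 adjusts for age and trait anxiety.

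**Working it through.** **Inputs from the article.** Three periods per participant (2.1); N = 84, 28 per stratum, d = 0.4, 90% power, two-sided 5% (2.2). The ICC, the dropout rate and the threshold-endurance correlation are not given, so they are assumed below.

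**The plan's own figure.** For a within-participant comparison, n = 2(1 − ICC)(1.960 + 1.282)²/d².

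- With ICC 0.5: 2 × 0.5 × 10.51/0.16 = 65.7, so 66 evaluable.
- With 20% dropout: 66/0.8 = 82.5, so 83, or 84 for three equal strata.

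Thus 84 is attainable but cannot be confirmed. With no dropout it would need an ICC of 0.36, with 10% dropout 0.42. The point does not depend on this.

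**Standard error of an education contrast, unadjusted.** With total SD 1, the variance of a participant's mean over three conditions is ICC + (1 − ICC)/3. At ICC 0.5 this is 0.5 + 0.5/3 = 0.667, an SD of 0.816. For 28 versus 28, SE = √(0.667 × 2/28) = 0.218.

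**Adjusted.** If r is the within-stratum correlation of threshold with mean endurance, the SE is multiplied by √(1 − r²). The equivalent gain in participants is 1/(1 − r²) − 1.

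| r (assumed) | SE factor | SE at ICC 0.5 | Equivalent extra participants |
|---|---|---|---|
| 0.1 | 0.995 | 0.217 | 1% |
| 0.3 | 0.954 | 0.208 | 10% |
| 0.5 | 0.866 | 0.189 | 33% |

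If r is instead defined against the person-level component alone, the variance is ICC(1 − r²) + (1 − ICC)/3. For ICC 0.4 to 0.9 the factor is then 0.96 to 0.97 at r = 0.3 and 0.87 to 0.91 at r = 0.5. Dropout would raise every SE but leave these ratios as they are.

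**Shift if strata differ in threshold.** The slope of mean endurance on threshold is r × 0.816 total SD per threshold SD (ICC 0.5). For an assumed stratum difference of 0.3 SD and r = 0.5, the shift is 0.3 × 0.5 × 0.816 = 0.12 total SD, against an SE of 0.218. At r = 0.3 it is 0.07 and at r = 0.1 it is 0.02.

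**Terms that do not change.** If a participant's endurance is a personal level (including sensitivity) plus a condition effect plus error, the difference between two of her conditions no longer contains the personal level. This holds for intervention contrasts and for comparisons of those contrasts between education groups. A simulation of 1,500 trials per setting (ICC 0.6, r from 0 to 0.7, threshold difference 0 or 0.5 SD) agreed:

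- The education-by-intervention contrast had an SE of about 0.24 and essentially no bias, with or without the threshold.
- With a 0.5 SD threshold difference, the unadjusted education main effect was off by 0.12, 0.19 and 0.27 SD at r = 0.3, 0.5 and 0.7. Adjustment brought this to about zero.

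**The case against.** **It misses the trial's question.** The stated aim and both hypotheses in section 3.2.1 concern whether the effect of music is the same across backgrounds. Those are within-participant contrasts and their interaction with background. A reader might infer that omitting the threshold weakens or biases them. The calculation shows that, under an additive model, it does not. This objection stands and confines the point to the main effects of background on endurance averaged over conditions. Those terms are nonetheless in the section 2.5 model and will be estimated.

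**Sensitivity may be a pathway.** A reader might also infer that a threshold difference between strata has nothing to do with culture and is pure bias. The documents do not support that. Education, occupation and income are not randomised, and electrical sensitivity could lie downstream of them. Adjusted and unadjusted coefficients then answer different questions. This stands, and it is why both should be reported.

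**The size is assumed.** The article gives no correlation and no stratum difference. At r = 0.1 the gain is negligible. The relevant r is also partial, given the covariates already in the model. This stands: the figures show a range and are not estimates.

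**Detail belongs in the analysis plan.** This does not stand. The article itself fixes the list of fixed effects, and the threshold is not in it.

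**Conclusion.** The point holds in a narrow form. A pre-intervention measure taken on the stimulation device is collected but does not enter the endurance model, and the between-participant education and background terms are where it could help. The gain in precision runs from negligible (0.5% at r = 0.1) to useful (13% at r = 0.5). The possible shift of an education contrast is about 0.12 total SD if strata differ by 0.3 SD in threshold, r = 0.5 and ICC 0.5. All of these inputs are assumptions.

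The omission is not an error in the trial's main comparison. It leaves the intervention contrasts unchanged when data are complete, and the consistency hypotheses unchanged under an additive model. Because the background analyses are exploratory, this is a minor, optional improvement.

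**What to change.** In section 2.5, add the sensation threshold as a fixed effect in the linear mixed model for pain endurance. Report the education and other background terms both with and without it, and say that the two versions differ in whether sensitivity is held constant. State that the intervention and intervention-by-background results are not expected to depend on this choice.

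On the same footing, the baseline STAI-6 and SAM scores may be added to the models for their own outcomes. The threshold need not enter the NRS models, since nothing above supports it there.

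The data are already planned for collection. The cost is a line or two of text, one degree of freedom for the threshold, and a second set of exploratory estimates to report.
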